## Methods

### Study overview

The study will establish “beacon sites” that will provide a network for wider-scale evaluation of roll-out in the NHS. Two therapists will be trained to deliver group MCT alongside CR at each of the participating sites.

A new data-field in National Audit of Cardiac Rehabilitation (NACR) database will be created to aid with data collection on the adoption of group MCT in CR. Routine Hospital Anxiety and Depression Scale (HADS) (32) data will be collected via the NACR database, which routinely contains HADS on patients pre- and post-CR.

Semi-structured interviews will be conducted with CR staff trained in MCT and CR stakeholders to assess the implementation of group MCT within CR services.

Our success criteria are:
1)Establishment of a minimum of three new beacon sites willing and able to support a large-scale roll-out study.2)Addition of an MCT field in the National Audit of Cardiac Rehabilitation (NACR) audit system and preliminary data on the quality of capturing group MCT related outcomes.3)Uptake of group MCT within services at each site will be based on delivering at least two six-session group MCT courses with 3–10 patients per group, with at least 60% attending at least four sessions.4)Identification of barriers and facilitators to implementation in the NHS in the areas of: - how is the intervention understood - how can it be translated into practice - how will it fit into services - how will it be sustained.

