### Data collection

We will add a rehabilitation delivery data field to the NACR database to include uptake of group MCT. In addition, routine outcomes from the NACR database will be collected, including anxiety and depression outcome data (i.e., the Hospital Anxiety and Depression scale), quality of life (i.e., Dartmouth Co-op), and clinical and demographic characteristics. Data will be captured from sites on attendance rates. In addition, CR staff will be asked to complete an adherence checklist to monitor adherence to the treatment protocol.

Qualitative data will be collected through semi-structured interviews completed either face-to-face, via Microsoft Teams, or by telephone. Interviews will follow a topic guide and will be audio recorded, anonymised, and transcribed verbatim. The interviews will be conducted with approximately 10 CR staff members trained in group MCT and 10 CR stakeholders (CR nurses, physiotherapists, occupational therapists, managers, and commissioners).

Participants will be prompted about their perspectives across four domains based on NPT, which include: sense-making (how the intervention is understood and compared with existing practices), implementation (how it is translated into practice), embedding (how will it fit routinely within services), and integration (how will it be sustained as part of routine practice).

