### Clinical outcome measures

The Hospital Anxiety and depression Scale [HADS (32)] is a 14-item self-report questionnaire that measures symptoms of anxiety (7 items) and depression (7 items). Items are rated using a 4-point (0–3) scale, with higher scores indicating elevated distress. Scores for each subscale range from 0 to 21 and can be categorised as normal (0–7), mild (8–10), moderate (11–14), or severe (15–21). The NACR pays an annual licence fee for HADS so that all NHS based CR programmes can use it free of charge.

The Dartmouth COOP (35) is a self-report measure designed to evaluate the functional abilities of medical patients. It consists of nine items covering various areas such as physical function, daily activities, pain, social activities, social support, emotions, overall health, changes in health, and quality of life. Each chart includes text and illustrations to assist the user in responding. The responses are graded on an ordinal scale of 1–5, with one being the best score.

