### Data analysis

#### Quantitative analysis

The Beacon sites and the NACR database will record patient attendance at group MCT. To assess if the modification to the NACR database successfully captures MCT attendance, descriptive statistics will be used to compare the data on patient attendance collected at the site level with that recorded in the NACR dataset.

To assess implementation of MCT at CR services an overall assessment will be made considering the traffic-light ratings of all beacon sites.

The NACR dataset collects a range of demographic, clinical, functional, and physiological measures on each CR patient, at both entry into CR and at discharge. The NACR data at entry will be used to describe the cohort of patients attending MCT and to compare their baseline characteristics to patients on CR only. The NACR data collected at discharge will be used to compare patient outcomes (HADS and Dartmouth Co-op etc.) between the cohorts (MCT + CR vs. CR alone). The analysis will control for a pre-specified set of baseline (entry) confounders: site, HADS, sex, age, number of comorbidities and number of previous different cardiovascular events. Sensitivity analysis will control for additional covariates that differed between the groups (MCT + CR vs. CR alone) above a specified threshold at entry. Further analysis will adjust for missing outcome scores at discharge. Caution will be exercised when interpreting the results as patients have not been randomised to groups hence systematic differences may exist due to unmeasured confounding factors. Therapist adherence to the MCT manual will be assessed using a checklist recording the treatment components implemented in each session, if any components had been missed, and if so, why. The list includes six to eight items for each session, covering the main techniques administered in each session. Session adherence scores will be computed by counting the total elements completed. Descriptive statistics will be used to assess adherence to the group MCT manual across Beacon sites. In addition, change in adherence over time will be compared between sites.

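### The main Dartmouth COOP comparison adjusts for entry HADS but not for entry Dartmouth COOP, which can enter only a threshold-triggered sensitivity analysis

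*Protocol article*

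**What the plan says.** All places are in the protocol article.

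- **Comparison** (Quantitative analysis): "The NACR data collected at discharge will be used to compare patient outcomes (HADS and Dartmouth Co-op etc.) between the cohorts".
- **Adjustment** (same section, next sentence): a "pre-specified set of baseline (entry) confounders: site, HADS, sex, age, number of comorbidities and number of previous different cardiovascular events". The list is enumerated, and nothing in it varies by outcome.
- **Further adjustment** (same section): a sensitivity analysis adds covariates on which the groups differ at entry by more than a threshold. The article does not print the threshold. A further analysis deals with outcome scores missing at discharge.
- **Data source**: Data collection lists, among routine NACR outcomes, "quality of life (i.e., Dartmouth Co-op), and clinical and demographic characteristics". Quantitative analysis says "The NACR dataset collects a range of demographic, clinical, functional, and physiological measures on each CR patient, at both entry into CR and at discharge". Clinical outcome measures describes the COOP as a "self-report measure designed to evaluate the functional abilities of medical patients". Study overview says of the NACR database, for HADS only, "which routinely contains HADS on patients pre- and post-CR".
- **Purpose** (Background, fourth research question): the effect of adding MCT on mental health and on quality of life.

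**The concern.** The printed set treats the two named outcomes unequally. Discharge HADS is compared given entry HADS. Discharge COOP is compared given entry HADS but not entry COOP.

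In a non-randomised comparison the entry value of an outcome is usually its strongest measured predictor and a leading confounder. Entry HADS can stand in for it only in part. HADS covers anxiety and depression, whereas the nine COOP items also cover physical function, pain, social support and overall health. Patients choose whether to join six face-to-face sessions, so function or pain could plausibly affect who attends.

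Any entry COOP difference that HADS and the other listed covariates do not explain passes into the estimated MCT effect. Its direction cannot be known in advance. The article's caution about unmeasured confounding does not cover this, because entry COOP appears to be measured.

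**Working it through.** The article gives no sample size, SD or correlation for this comparison, so there is no stated figure to reproduce. The calculation below shows size only, and every correlation and imbalance in it is an assumption.

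**Set-up.** All scores are standardised to SD 1.
- r = correlation of entry COOP with discharge COOP, taken as 0.4 to 0.7
- h = correlation of entry COOP with entry HADS, taken as 0.3 to 0.7
- g = correlation of entry HADS with discharge COOP, taken as 0.3 to 0.5 and not above r
- d = entry COOP difference between groups that remains after HADS adjustment

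**Formulas** (linear regression with two predictors)
- Residual variance, HADS only: V1 = 1 − g²
- Residual variance, HADS and entry COOP: V2 = 1 − (r² + g² − 2rgh)/(1 − h²)
- SE inflation from leaving out entry COOP: √(V1/V2)
- Slope of discharge COOP on entry COOP given HADS: b = (r − gh)/(1 − h²)
- Bias from leaving out entry COOP: b × d

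**Middle case, r = 0.6, h = 0.5, g = 0.4**
- V1 = 1 − 0.16 = 0.84
- V2 = 1 − (0.36 + 0.16 − 0.24)/0.75 = 1 − 0.373 = 0.627
- V1/V2 = 1.34, and √1.34 = 1.16, so the SE is 16% larger
- b = (0.6 − 0.2)/0.75 = 0.533, so the bias is 0.11 SD at d = 0.2 and 0.05 SD at d = 0.1

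**Range**

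| Case | r, h, g | V1 | V2 | SE inflation | b | Bias, d = 0.2 | Bias, d = 0.1 |
|---|---|---|---|---|---|---|---|
| Lowest | 0.4, 0.7, 0.4 | 0.840 | 0.812 | 2% | 0.235 | 0.05 | 0.02 |
| Middle | 0.6, 0.5, 0.4 | 0.840 | 0.627 | 16% | 0.533 | 0.11 | 0.05 |
| Highest | 0.7, 0.7, 0.3 | 0.910 | 0.439 | 44% | 0.961 | 0.19 | 0.10 |

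**Does the threshold rule catch it?** Bias is slope times gap, but a rule on entry differences looks only at the gap. In the table, a 0.1 SD gap with the highest slope gives 0.10 SD of bias, while a 0.2 SD gap with the lowest slope gives 0.05 SD. The smaller gap does more harm, and it is the less likely of the two to trigger the rule.

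**Limits of the calculation.** It leaves out age, sex, site, comorbidity count and cardiovascular-event count, which may explain part of entry COOP. It treats the COOP as one continuous score, although its items are ordinal from 1 to 5. The SE figures also ignore the small cost of adding a covariate related to group. With equal groups and d = 0.2, the between-group variance of entry COOP is 0.25 × 0.2² = 0.01. The cost is then about 0.01/(0.91 + 0.01) = 1% of variance at h = 0.3 and 0.01/(0.51 + 0.01) = 2% at h = 0.7. This matters only at the bottom of the range.

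**The case against.** **The plan already has a route for entry COOP.** A reader might infer that the COOP comparison is never adjusted for its entry value. The article does not support that, because a COOP difference above the threshold would bring it into the sensitivity analysis. If MCT patients also have worse entry HADS, the raw COOP gap would exceed the gap left after HADS adjustment, so large imbalances would probably be flagged. This much stands. But the route depends on the data, leaves the main estimate as it was, and gives no precision when the gap falls below the threshold.

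**Entry COOP is not named as available.** This stands in part. Only HADS is said by name to be held before and after CR. Entry COOP is an inference from three statements: the COOP is a routine NACR outcome, it measures function, and NACR takes functional measures "at both entry into CR and at discharge". The inference is strong, but it should be confirmed with NACR.

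**A condensed article may leave covariates to the analysis plan.** This does not answer the point. The article prints the list and calls it pre-specified. If a fuller document adds outcome-specific entry values, the published list needs the same correction.

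**The stakes are limited.** This is fair. None of the four success criteria uses the COOP, and the article twice warns about unmeasured confounding. Even so, quality of life is part of the fourth research question.

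**Conclusion.** The point holds for the main analysis. The Dartmouth COOP comparison is adjusted for entry HADS but not for entry COOP, which leaves avoidable confounding and lost precision in the quality-of-life part of the fourth research question.

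The documents do not fix the size. Under the assumed correlations the bias is about 0.05 to 0.19 SD per 0.2 SD of remaining entry imbalance (middle case 0.11), and the SE is inflated by about 2% to 44% (middle case 16%). For scale only, the article reports PATHWAY effects on HADS, a different outcome, of 0.52 and 0.33 SD.

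A reader might go further and conclude that the quality-of-life result will be biased by a known amount or in a known direction. Nothing in the article supports that: it gives no entry COOP gap and no correlations. The HADS comparison is not affected, since its own entry value is in the set. Unmeasured confounding would remain after the change.

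**What to change.** Add *the entry value of the outcome being analysed* to the pre-specified set, keeping entry HADS and the other listed covariates. Apply it to the COOP and to any other NACR outcome measured at entry. Make an exception for the COOP item that rates change in health: its entry rating is already a rating of change and not a true baseline for the discharge rating.

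The cost is one phrase in the covariate list and, if NACR holds entry COOP as the article implies, no new data collection. The one downside is that some patients may lack an entry COOP score. The stated missing-data step covers discharge outcome scores only, so it cannot be assumed to deal with them. The plan should say how missing entry scores are handled, for example by imputation, so that these patients are not dropped from the main model.

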#### Qualitative analysis

Qualitative analysis will use thematic analysis as outlined by Braun and Clarke (37). Initial codes will be genereated inductively, and not driven by a pre-determined framework. Each transcript will be coded based on the study aims. We will subsequently draw on the NPT framework (26) to help consider implications for assimilating the intervention into existing practice. The researcher will lead the analysis, using constant comparison to cycle between data and the developing analytic framework, working with a core analysis team (research assistant/research fellow) who will read all transcripts. The analysis will be tested and developed by discussion regularly with the broader study team.

## Discussion

MCT is a psychological intervention that has the potential to significantly improve psychological outcomes in patients with CVD and offer added choice and value over standard healthcare practices. The mental health benefits would be substantial if MCT could be provided to the 90,000 patients in the United Kingdom commencing CR annually. However, there are significant recognized challenges to implementing and rolling out complex interventions of this kind. We propose a study that will allow us to create the data-monitoring structure and knowledgebase across beacon sites and evaluate data quality and the real-world effects of implementing MCT. The findings will allow us to adapt and modify data capture and monitoring and better understand group MCT training and delivery to facilitate its implementation in cardiac rehabilitation services. The use of quantitative and qualitative methods will generate data to inform and prepare for potential roll-out and evaluation across CR services in the NHS.

Our quantitative work will provide data on the quality of data-capture, the level of adoption at NHS sites, adherence to the treatment protocol and sociodemographic and heath differences between patients who take-up MCT and those who do not. It will assess performance on key outcomes benchmarked against treatment as usual; however, these results must be interpreted with caution: there will be no randomisation hence estimated group differences – even after control for known factors – will be subject to unmeasured confounding. The qualitative stream will develop an account of the influences on training and barriers and facilitators to implementation that has implications for maximising engagement. Use of the NPT framework will facilitate examination of the factors important for embedding MCT within existing services.
